## Abstract

**Background:**

Serious mental illness (SMI) is a prevalent public health problem affecting 25% of individuals in jail. Re-entry to the community following incarceration is a vulnerable time for justice-involved individuals with SMI. SMI requires prompt and ongoing access to mental health and other healthcare services.

**Methods:**

The study will (1) develop a Mentoring And Peer Support (MAPS) intervention for post-release mental health and other service connection among jailed individuals with SMI and (2) pilot test the MAPS intervention to determine its feasibility and acceptability. The primary outcomes will be to evaluate the feasibility and acceptability of the proposed recruitment methods and research design, of the intervention training methods, and of delivering the enhanced peer-navigator and control interventions. Study samples include focus groups (n=36), open trial (n=15), and a randomized pilot trial in a sample of 40 individuals with SMI re-entering the community after jail release. Secondary outcomes will include post-release enrollment in mental health, medical care, and substance use services. We will also evaluate reduction in psychiatric symptoms, improvements in functioning, adherence to psychiatric medications, fewer substance using days, fewer hospitalizations and suicide attempts, nights unstably housed, and time until rearrest.

**Discussion:**

This pilot study will evaluate the feasibility and acceptability of a peer navigation intervention for individuals with serious mental illness leaving jails. The study will serve as a formative work for a larger randomized controlled trial assessing the effectiveness of peer navigator intervention for (include the primary outcome) in this population.

## Background

The US criminal justice system contributes to 22% of the world’s incarcerated population [1]. Approximately 12 million people in the US become or are incarcerated each year. Among these, individuals with serious mental illnesses (SMI; psychotic and affective disorders associated with functional impairment and interference with major life activities) are disproportionately represented, accounting for 25% of the justice-involved population [2–4].

Re-entry to the community following incarceration is a vulnerable time for justice-involved individuals with SMI. They experience multiple barriers to accessing mental health, medical care (preventive and curative), and social services due to debilitating symptoms, practical challenges accessing community services, and the stigma associated with being diagnosed with SMI [5, 6]. Potential consequences of lack of care include exacerbation of psychiatric symptoms, substance use relapse, homelessness, and repeat incarceration [6–8].

Peer navigation has been found to improve access to mental health services and medical care among non-justice involved individuals [9, 10]. Peer navigators are individuals who have successfully overcome an adverse life experience and whose lived experiences and formal trainings [11] are believed to support or encourage others in similar situations [12]. Peer navigators share life experiences with their clients such as a diagnosis of SMI or a history of CJ involvement, making them credible and persuasive as navigators than non-peer navigators [13]. Peer-provided services are positively regarded and accepted and are often preferred by individuals with SMI because they demonstrate better understanding compared to regular case managers [14]. Three previous studies of non-justice involved individuals with SMI found that SMI peer navigators increase adherence to psychotropic medications [15] and medical and mental health care utilization [16, 17].

No peer support interventions have been tested to assist with mental health service linkage for individuals with SMI during re-entry to the community after jail incarceration. One study of substance use peer navigators during community re-entry (not among individuals with SMI) has shown that using a peer navigator model during re-entry is feasible [5]. The purpose of the proposed study is to develop a peer navigator intervention for mental health, substance use, and medical care treatment engagement among justice-involved individuals with SMI who are re-entering the community after jail incarceration and to then evaluate its feasibility, acceptability, and ways the intervention contributed to the desired outcomes.

In this study, peer navigators will be trained individuals who share the joint experience of having the diagnosis of SMI and also having a history of justice involvement. Their lived experience as someone diagnosed with SMI and familiarity with the justice system makes them ideal practical supports for facilitating prompt and ongoing access to mental health, medical care, and substance use services for others at community re-entry.

This pilot study will provide formative work for a larger randomized controlled trial evaluating the effectiveness of peer navigator intervention for justice-involved individuals with SMI. The study will have two phases. The first (development) phase aims to (1) enhance and tailor a peer-navigator intervention for justice-involved individuals with SMI re-entering the community using qualitative research; (2) develop, implement, and evaluate the intervention training program using qualitative and quantitative techniques; and (3) improve the clarity, content, acceptability, and feasibility of the tailored peer navigator intervention through a small open trial (*n* = 15) of justice-involved individuals with SMI re-entering the community. The second (pilot study) phase aims to conduct a randomized pilot trial in a sample of 40 justice-involved individuals with SMI who are anticipating jail release in the next 30 days. The control condition will be Standard of Care (SOC). Study assessments will take place at baseline, 3 months, and 6 months after release. The goal is to demonstrate the feasibility and acceptability of the proposed recruitment methods and research design, of the intervention training methods, and of delivering the enhanced peer-navigator and control interventions.

This study protocol describes the planned process of development of a peer navigation intervention for creating linkages to mental health, medical care, and substance use services. We also present plans for evaluation of feasibility, acceptability, and potential engagement of target mechanisms of a peer navigation intervention for justice-involved individuals with SMI who are re-entering the community after jail release.

## Methods

### Development phase

#### Project advisory board

In collaboration with our local community mental health system (Genesee Health System; GHS), we will establish a project advisory board of 6–8 justice-involved individuals with SMI who have served as peer navigators or supervisors in other settings. We will also include individuals who have served as peer mentors for justice-involved individuals with SMI. Our advisory board members will provide periodic input throughout the project, including providing their pragmatic experiences to guide manual adaptation and study recruitment.

#### Manual development

We will draw content from the Chicago Health Disparities Center (CHDC) peer navigators’ training manual developed for homeless African Americans with SMI and adapt it for use by justice-involved individuals with SMI. The CHDC manual was designed to help clients engage with and benefit from primary care. This manual will be our starting document because it has a strong evidence base [9, 16] and was found to be effective in linking a marginalized SMI population to primary care services [16]. Adaptation of the CHDC manual will involve keeping the basic structures and principles of the peer navigation intervention and expanding the manual to include re-entry specific components described in Table 1 below.

**Table 1 Tab1:** The MAPS intervention manual

	Current contents	Population specific additions
**Instrumental support** for treatment engagement and recovery	Principles in helping relationships Basic helper principles in your life Advocacy Engaging people through goal setting	Steps to peer navigation before anticipated date of release Assist with completion of important paperwork Link individuals with organizations that provide ID services Ensure access to transportation Housing, employment, etc. in the context of a criminal record
**Informational support** for tx engagement and recovery	Provide information about food pantries Inform clients about sliding scale and fee waivers	Information about treatment options for SMI Help clients identify appropriate providers Information on accessing mental health, medical, and substance use care
**Emotional support** for tx engagement and recovery	Reflective listening skills Strengths-based model	Unconditional acceptance and reassurance Adherence support (encouraging adherence) Going with clients to agencies to provide emotional and practical support
**Social norms** around treatment engagement and recovery	Setting boundaries Managing burnout The big picture	Sharing own experiences with SMI and justice involvement Working with the justice system Acting as role models

The manual will be adapted and expanded to include specific information related to working with justice-involved individuals with SMI and potential ways to effectively engage with them after re-entry (see Table 1). For example, content related to working with the justice system, how to assist with paperwork, the art of self-disclosure, meeting basic needs of clients (i.e., housing, food), identifying providers, and access to community services will be added.

#### Focus group discussions

We will conduct focus group discussions (FGDs) to aid in manual development and to provide feedback to help ensure that the MAPS peer navigation intervention meets the needs of our target population. Five FGDs of 6–8 people each (for 30–40 people total) will be conducted: 2 groups with experienced peer navigators and 3 groups with individuals in jail with SMI. The FGDs will explore perspectives of potential clients and peer navigators regarding the effectiveness, acceptability, and gender and cultural appropriateness of peer navigator intervention and the most important approaches for them to take with justice-involved individuals with SMI. FGDs with peer navigators will ask about: (1) the most essential peer navigation skills, (2) lessons they have learned in their careers to date, (3) local services for individuals re-entering the community, and (4) how to initiate and maintain a culturally competent peer navigation service for individuals re-entering the community. We will also interview 4 peer navigators working with prisons from other states to understand experiences across the country using the topic guide described above. With potential client groups, we will explore (1) how peer navigators can best gain their trust, (2) their greatest needs in overcoming barriers to (post-release) treatment engagement, (3) what would assist their treatment engagement and how peer navigators could help with that, and (4) feedback on the proposed MAPS intervention outline. To understand the challenges after re-entry, we will include participants who have had re-entry experiences. The peer navigators’ focus group discussions will focus on how peer navigators can best help participants overcome misconceptions, mental health stigma, and other barriers to service linkage.

We will conduct qualitative coding and analysis of FGD data. FGDs will be facilitated by a moderator and a note taker. FGDs will be audio-recorded. The audio files will be transcribed verbatim. With the assistance of the Co-investigators, the Principal Investigator will lead the qualitative analysis and interpretation. Major topics and sub-topics will be coded. Additional codes will be generated for topics that invariably arise and that may have significance to the project. A descriptive summary will be developed to represent key content of each FGD. To enhance rigor and facilitate the quality of data management, we will use NVIVO version 12 [18]. We will conduct member checking with selected study participants to validate the fit, credibility, and transferability of the results from the FGDs. We will use a framework analysis technique [19]. We will create the coding framework in the NVivo structure, and coders will chart data into the provided framework. We will refine and adapt our intervention for our target population based on the recommendations of focus group participants.

#### Open pilot trial

We will conduct an open pilot trial with 15 justice-involved individuals with SMI who meet the same inclusion criteria as participants in the randomized trial. Participants will complete all research procedures (see below) and receive MAPS, allowing us to gain experience with and assess the feasibility of the intervention, strategies for recruitment and retention of participants, recruitment and supervision of peer navigators, and participants’ compliance with the study protocol. Participants will be requested to complete an intervention-specific End-of-Treatment Questionnaire [20] assessing perceived helpfulness of the intervention and their comfort with the research processes and assessments. We will also conduct exit interviews with participants and peer navigators. In the exit interviews, we will collect information on what went well, what needs to be improved or added to the manual.

During the open trial, we will carefully evaluate and document our training methods, recruitment and retention procedures, and the fit and adaptability of the treatment manual. We will collect data on what went well and what needs to be improved. We will use our experiences with the recruitment process, intervention, participant tracing, follow-up assessments, data from training of peer navigators, the End-of-Treatment Questionnaire, and feedback from the exit interviews to further refine the manual.

### Pilot study phase

#### Study design and setting

The study will be conducted in Genesee County in Flint, Michigan. We partnered with Office of the Genesee County Sheriff and the Genesee Health System, a community mental health center in Genesee County. The study participants will be recruited from Genesee County Jail and from a network of peer navigators working with the Genesee Health System.

#### Sampling and recruitment

The open trial (*n* = 15) and randomized pilot study (*n* = 40) will use the same broad inclusion criteria. Participants will be (1) incarcerated in the Genesee County Jail, (2) aged 18 or above, (3) with lifetime DSM-5 diagnosis of SMI (including primary psychotic disorder [schizophrenia, schizoaffective disorder, or delusional disorder], bipolar disorder, and/or a major depressive disorder with psychotic features) as assessed by the Structured Clinical Interview for DSM-5 (SCID-5) [21], and (4) anticipating release in the following 2 months. We will exclude individuals who (1) expect to be sentenced to prison (i.e., expect to go directly to prison, not home, from the jail), (2) cannot provide name and contact information of at least two locator persons, and/or (3) do not have access to any telephone. Some individuals are intoxicated, high, manic, and/or experiencing active psychosis when arrested and brought to the jail. We will exclude individuals who are too impaired to provide informed consent (i.e., are unable to respond coherently to the screening and consent process). If someone reports being or appears to be intoxicated or high, screening and consent procedures will be postponed until later, and jail protocols for referral to care will be followed.

The study research assistant (RA) will consent and screen potential participants privately. The RA will explain all aspects of the study, including confidentiality and its limits, and address questions. If the participant agrees, s/he will sign an informed consent form and complete the baseline assessment. The RA will offer to read the consent forms aloud. The RA will emphasize that enrollment in the study is completely voluntary. Those who consent to participate will be provided with a copy of the study information sheet and an informed consent document. The peer navigators have no role in the study assessments.

#### The control condition

The control condition for this study will be Standard of Care (SOC). SOC consists of SOC + monitoring and emergency referral, as is required to fulfill ethical obligations to trial participants. To determine the naturalistic effects and costs of adding peer navigation intervention, participants in both conditions can receive any other treatment available to them. Participants who may be receiving other treatments will not be excluded. As part of our service utilization assessment, we will carefully characterize SOC for each condition.

#### The intervention

The peer navigation intervention is based on social support theory [22]. Peer navigators will help participants overcome the significant structural barriers to treatment engagement at community re-entry by providing instrumental (i.e., practical), informational, and emotional support for treatment engagement through activities such as helping with the referral navigation process, keeping track of appointments and paperwork, following up with clients to make sure they went to appointments, problem-solving challenges, providing information about free care, helping clients make informed decisions about care by providing patient education, and creating peer connections. In addition, sharing their own stories of treatment and recovery and acting as role models shifts social norms toward treatment engagement and recovery [16, 23].

Participants assigned to the intervention group will receive the MAPS peer navigation intervention for 6 months (1 month pre-release, 5 months post-release). Approximately a month before release, the study research assistant will introduce consenting eligible individuals to a peer navigator who will help them navigate through community mental health, medical care, or substance use services. All peer navigators will disclose their history of criminal justice involvement, SMI, and/or co-morbid substance use during the initial introduction. In the weeks before release, the peer navigators will meet their clients at private locations within the jail to conduct strengths and needs assessments, fill out insurance forms, provide information on steps required to establish their insurance eligibility and residence IDs, and help set up community treatment appointments as needed. Peer navigators will maintain regular contact with participants at least once a week in the jail until they are released. Information obtained as part of the pre-release visits will be used to plan the rest of the peer navigation process after re-entry.

After re-entry, peer navigators will meet with their clients (in person or by phone) up to three times a week in the first 2 months and once a week in the following 3 months after release for a session no less than 60 min. Peer navigators will meet their clients within the first week of re-entry, preferably within the first 24–72 h after release. In-person meetings will take place in the community at safe locations convenient for participants (i.e., libraries, treatment facilities, public buildings). The peer navigators will review participants’ activities since they left jail and problem-solve any barriers to service linkage or access that might have occurred. If clients have an outstanding referral to health care providers, the peer navigator will go with the client (whenever requested) or facilitate their trip to a provider by helping them get bus tickets or identify other reliable means of transportation. Peer navigators will meet with their clients depending on their need and jointly established treatment plan. Their services will involve (1) providing instrumental support for treatment engagement and recovery by focusing on strengths, being a role model and sharing personal experience, show genuine concern, identify stressors and roadblock and link to self-help [24]; (2) sharing information about treatment engagement, creating service linkages after involvement with the justice system, health and lifestyle changes required to promote recovery, and information about access to free treatment options [25, 26]; and (3) fostering emotional support for treatment engagement by showing empathy, promoting empowerment/hope, and facilitating trust in treatment providers [24, 27]. In addition to the weekly meetings with their clients, peer navigators will do a monthly progress evaluation and refine treatment plans accordingly. See the flow chart (Fig. 1) for the planned randomized trial below.

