#### Peer navigator training and supervision

We will recruit 4 peer navigators (3 males, 1 female) and train them to fidelity to deliver the intervention. The 4 half-day long, didactic in-person initial trainings will consist of reviewing the peer navigation intervention rationale, materials, and strategies; audio-taped demonstrations; and live practice sessions with feedback. Weekly group supervision meetings will be held with peer navigators via phone or in-person to assist with any outstanding concerns. All peer navigation sessions will be audiotaped. Supervision will involve review of peer navigators’ audiotaped sessions (with fidelity rating as appropriate), group supervision and case discussion, and individual phone consultation as needed.

We will employ several approaches that we have found helpful in achieving low attrition rates (0–20%) in previous intervention studies with individuals re-entering the community after incarceration [28–31] (including those who were homeless) and other high-risk samples [32, 33]. These include study staff’s strong relationships with participants and efforts to value and appreciate their study participation. The study research assistant will call participants and mail them letters to remind them of their appointments and maintain a list of 2 other people who will always know where participants reside. Locator information will be updated at each study contact. Telephone follow-up assessment (removing the need for transportation) and study team flexibility in scheduling follow-up assessments (i.e., on evenings or weekends) will also facilitate participant retention. Finally, participants will be remunerated $50 for each follow-up assessment, facilitating retention.

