**Life context outcomes**

We will use a calendar-based interview method [44–50] to measure number of nights unstably housed and days until rearrest.

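### The research assistant's introduction of MAPS participants to their navigator reveals the arm to the staff role most likely to do the follow-up interviews

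*Protocol article*

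**What the plan says.** Four parts of the Protocol article bear on this.

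- **Enrolment (Sampling and recruitment).** "The study research assistant (RA) will consent and screen potential participants privately". Baseline follows consent: "If the participant agrees, s/he will sign an informed consent form and complete the baseline assessment". The section then separates delivery from assessment for one group: "The peer navigators have no role in the study assessments".
- **Start of the intervention (The intervention).** In the paragraph on those assigned to MAPS: "Approximately a month before release, the study research assistant will introduce consenting eligible individuals to a peer navigator".
- **Follow-up contact (Peer navigator training and supervision).** "The study research assistant will call participants and mail them letters to remind them of their appointments". The research assistant also keeps the list of people who know where each participant lives. The assessments themselves are described without naming who does them: "Telephone follow-up assessment (removing the need for transportation) and study team flexibility in scheduling follow-up assessments".
- **Outcomes (Secondary outcomes, Life context outcomes, Table 3).** Hospitalisations and mental health service use come from the Treatment History Interview (THI). For unstable housing and rearrest: "We will use a calendar-based interview method". Table 3 places the support measures at baseline, 3 and 6 months, and the CSQ-8, ETQ and WAI at 6 months.

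**The concern.** Participants cannot be blinded to having a navigator, so the interviewer is the main point at which this trial can keep knowledge of the arm out of the data. The article sees the risk, since it keeps navigators away from assessment. It then gives a delivery step to the research assistant, the only staff role it names for enrolment and follow-up contact.

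The outcomes most exposed are those obtained by interview. A recalled count of appointments, admissions or nights unstably housed depends on how hard the interviewer probes and how doubtful entries are resolved. The number of outpatient mental health appointments is analysed first among the secondary outcomes, and the Target mechanisms analysis treats it as the main outcome. If probing differed by arm, its effect size would mix a measurement difference with any effect of MAPS, and 40 participants give no means of separating the two. That estimate is part of what the pilot hands to the full trial.

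**Working it through.** No figure in the documents measures this bias, so the check is mainly a matter of tracing who knows what, and when.

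**Step 1: does the research assistant learn the arm?** Yes. The introduction is described for MAPS participants, and control participants have no navigator to meet. Making an introduction identifies MAPS; not being asked to make one points to control.

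**Step 2: when?** About a month before release. Follow-up is at 3 and 6 months after release, so the arm is known before any follow-up outcome exists. Baseline follows consent and on the natural reading precedes the introduction, so baseline data are not clearly exposed.

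**Step 3: does this role do the follow-up interviews?** Not stated. The research assistant is given reminder calls, letters and the locator list. Assessment is by telephone, and its scheduling is attributed to the study team. No other assessor role is named. It is likely, not established, that the research assistant interviews.

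**Step 4: which outcomes would be affected?** The THI and the calendar interview are interviews by name, and effect sizes or exploratory between-arm comparisons are planned from both. The case does not extend to:
- C-SSRS: suicide attempts are not in the Data analysis list of between-arm effect sizes;
- BARS: described as counts of doses and days, with nothing about interviewer judgement;
- ASRM: a self-rating scale by name.

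**Step 5: could even a blinded interviewer learn the arm?** Yes. The WAI is used to assess the relationship with the navigator, and the CSQ-8 and ETQ ask about the intervention. Answers on instrumental, informational and emotional support, collected at 3 and 6 months, could also disclose a navigator. The article states no order of administration.

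**Step 6: scale, as illustration only.** First the plan's own figure. With 20 per arm, two-sided alpha .05 and a two-sample t-test, the noncentrality at d = .91 is 0.91 / √(1/20 + 1/20) = 0.91 / 0.316 = 2.88. That gives power 0.801, and the detectable d at power .80 is 0.909. The stated d = .91 is reproduced.

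Now assume an arm-related shift b in a measured outcome. The estimated effect size becomes the true one plus b. With no true effect, the rejection rate of the same test is:

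| Assumed shift b (SD) | Rejection rate |
|---|---|
| 0 | 5% |
| 0.1 | about 6% |
| 0.2 | about 9% |
| 0.3 | about 15% |
| 0.5 | about 34% |

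For comparison, the 95% interval for an effect size near zero has a half-width of about 1.96 × 0.316 = 0.62. A shift of 0.1 to 0.3 SD would therefore sit well inside the sampling error of this pilot. The values of b are assumptions without support in the documents, and the t-test is simpler than the planned mixed models. The table shows how a shift would act, not that one of this size is present.

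**The case against.** The strongest objection is that a reader might infer the follow-up outcomes are in fact collected by someone who knows the arm. The documents do not support that. They nowhere name the 3- and 6-month interviewer, and a research assistant who makes introductions and sends reminders is compatible with a separate blinded interviewer. Blinding of assessors is also something a condensed article may leave to the full protocol, so silence on it is no finding. This stands, and it limits the point to a conditional one. It does not remove it, because the introduction is a stated step and not a gap in the text.

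A reader might also infer an interviewer with a close personal tie to participants. The article does rely on "strong relationships with participants and efforts to value and appreciate their study participation", but attributes this to study staff generally, not to the research assistant or to any assessor. It should not be used to strengthen the argument.

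Third, appointments, admissions and rearrest are counts or dates, not ratings. That reduces the room for judgement but does not close it, because the named method for obtaining them is an interview.

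Finally, the trial is a pilot whose primary outcomes are feasibility and acceptability, with between-arm tests labelled exploratory. This stands and settles the severity. It is not a complete answer, because the Data analysis section puts its emphasis on the direction and range of between-arm effects, and feasibility of the research design is itself a primary outcome.

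**Conclusion.** The point holds in conditional form. It is established that the research assistant learns the arm before any follow-up outcome is collected, that this is the only staff role named for consent, screening and follow-up contact, and that the stated safeguard covers only the navigators. If this role also conducts the 3- and 6-month interviews, which is likely but unstated, the THI outcomes (service use, hospitalisations) and the calendar outcomes (housing, rearrest) would be collected with knowledge of the arm.

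The direction and size of any resulting bias cannot be estimated from the documents. Severity is low: no primary outcome depends on a between-arm comparison, and at 20 per arm sampling error is wide. The point is worth acting on because the pilot's effect sizes are meant to inform the full trial and the remedy is cheap.

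**What to change.** 1. State who conducts the 3- and 6-month interviews and whether that person knows the arm.
2. Have the navigator, who already meets clients in the jail, or the navigator supervisor make the introduction after allocation. Keep allocation from whoever conducts the follow-up interviews.
3. At the start of each follow-up call, ask participants not to mention a navigator.
4. Complete the THI and the calendar interview first. Give the measures likely to reveal the arm last: the support measures at 3 and 6 months, and the CSQ-8, ETQ and WAI at 6 months.
5. Record the interviewer's guess of the arm after the two interviews and before those last forms.

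No staff, visits or participants are added. The cost is a small change in jail logistics and a fixed order for the calls. Some unblinding will remain because participants will let things slip. The recorded guess measures how much, and gives the full trial a feasibility figure on blinded assessment. If a separate blinded interviewer is already planned, a sentence saying so meets item 1 and the introduction can stay as it is; items 3 to 5 are still useful.
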